### Assessment descriptions for clinical outcomes

#### Qualitative assessments

##### Ethnographic research

Ethnographic non-participant observations of a selection of the 12 workshops including at least 1–2 groups from each of the two phases (building confidence, rehearsal and production) to capture facilitator and participant practice, interactions and routines. Each observation period will last for the duration of the workshop, and the ethnographic researcher will record field notes contemporaneously.

##### Semistructured interviews

Semistructured interviews will be held with facilitators and participants’ pre and postprogramme cycles to explore anticipated concerns and expectations (pre) and experiences of facilitation and factors influencing delivery, engagement of participants, adaptation and learning (post).

The implementation science research team will be interviewing participants across both, the 12-week programme and ambassador training, in addition to wider stakeholders.

### Assessment descriptions for the implementation outcomes

#### Quantitative assessments

Validated and standardised implementation scales will be used to gather quantitative data on how acceptable, appropriate and feasible the SO programme is perceived by stroke survivors, ambassadors, deliverers, supporters and referrers. These scales include the Acceptability of Programme Measure (AIM), the Programme Appropriateness Measure (IAM) and the Feasibility of Programme Measure (FIM). For further information on the development of these scales, please refer to the paper by Weiner *et al*.^24^

The implementation science researchers will quantify and cost the resources used in implementing the programme, evaluate wider service utilisation and associated costs before and after participants complete the programme, including any changes to their quality-of-life profile measured using the EQ5D-3L preference-based QoL measure. The EQ5D-3L is a self-complete multiattribute measure of health-related quality of life that assigns individuals a unique state of health based on their response to individual items. Each unique health state is associated with a predetermined ‘utility’ value derived from a survey of wider community preferences over different states of health. The utility scale is anchored at 1 (full health) and zero (death), with negative values allowed in instances where states of health are considered worse than death. Health state utility values are subsequently used to estimate quality-adjusted life years (QALYs) survived over time—the utility scores providing the means of making the quality adjustments. Evidence on costs and QALYs will subsequently be used to inform an analysis of the cost-effectiveness of programme delivery at scale.

#### Qualitative data collection

##### Semistructured interviews

Semistructured interviews will be conducted with a purposive subsample of stroke survivors (N=20: 5 from each cycle at two time points—T2 and T3). Interviews will be carried out with this subsample of stroke survivors to explore their attitudes towards the acceptability, appropriateness and feasibility of the programme as well as factors (facilitators or barriers) that affected their involvement (and potential drop-out) and any unintended consequences. These issues will also be explored with a subsample of individuals (10 in total) from each of the wider stakeholder groups.

Interview guides have been based on the existing implementation frameworks (see above) and adapted from a previous project.^25^ They will be further adapted and codesigned with our stakeholder group to ensure the questions in the interview guide are meaningful and address the core aims of the study.

Interviews will be audiotaped and are anticipated to be conducted 1:1 or in participants dyads, face to face (government guidelines permitting) or remotely by phone or video.

### Data analysis

Data will be analysed using quantitative and qualitative approaches.

#### Quantitative analysis

Descriptive statistics of survey data will be performed (frequency distribution, central tendency). Parametric and non-parametric tests will also be employed to compare the survey responses to the AIM, FIM, IAM and EQ5D before and after the SO intervention. Changes in AIM, FIM, IAM and EQ5D will be assessed using generalised linear models depending on the distribution of the outcome (continuous, binary, ordinal). All analyses will be conducted in STATA V.14.1.

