**Primary objective**				
To evaluate to what extent SO is acceptable, to survivors and wider stakeholders	Acceptability of intervention Measure Semi-structured interviews (to explore reasons for acceptability score)	Quantitative Qualitative	T1, T2, T3 T2, T3	Stroke survivors, deliverers, supporters, referrers Stroke survivors, deliverers, supporters, referrers

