**Secondary objectives**				
To evaluate to what extent SO are appropriate to survivors and wider stakeholders	Intervention Appropriateness Measure Semi-structured interviews (to explore reasons for appropriateness score)	Quantitative Qualitative	T1, T2, T3 T2, T3	Stroke survivors, deliverers, supporters, referrers Stroke survivors, deliverers, supporters, referrers
To evaluate to what extent Stroke Odysseys feasible to survivors and wider stakeholders	Feasibility Intervention Measure Semi-structured interviews (to explore reasons for feasibility score)	Quantitative Qualitative	T1, T2, T3 T2, T3	Stroke survivors, deliverers, supporters, referrers Stroke survivors, deliverers, supporters, referrers
To assess any unintended consequences of the programme	Semi-structured interviews	Qualitative	T2, T3	Stroke survivors, deliverers, supporters, referrers
To explore the facilitators and barriers to implementing the programme	Semi-structured interviews	Qualitative	T2, T3	Stroke survivors, deliverers, supporters, referrers
To explore the facilitators and barriers to sustained use of the programme	Semi-structured interviews	Qualitative	T2, T3	Stroke survivors, deliverers, supporters, referrers
To assess service utilisation and cost associated costs and changes in quality of life associated with the implementation of the programme	EQ5D-5L (quality of life measure) and AD-SUS (adult service receipt schedule) and semi-structured interviews and activity data (to estimate implementation costs).	Quantitative	T2 and T3	Stroke survivors Stroke survivors, deliverers, supporters, referrers
To explore the strategies including resource inputs used, used within individual sites to implement the programme	Semi-structured interviews	Qualitative	T2, T3	Deliverers, referrers
To assess the adoption of the programme	The number of individuals delivering the programme, and the number of individuals supporting the programme (and continuing to do so)	Quantitative	T0, T2, T3	Deliverers, referrers
To assess programme adherence and attrition rates	Data on the overall adherence to the programme, number of drops-outs and reasons why	Quantitative Qualitative	Data recorded from the register on weekly attendance rates for the 12 week programme (stage 1) and 4 week ambassador programme (stage 2) T2, T3	Deliverers (record data) Stroke survivors

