### Outcomes

Data on the clinical outcomes will be collected from stroke survivors who have enrolled on the SO programme (see table 1). Data on the implementation outcomes will be collected from stroke survivors who have enrolled on the SO programme as well as the wider stakeholder group involved in the SO programme, including deliverers, referrers and supporters (see table 2).

Time points for data collection: T0—baseline; T1—midway through the 12-week programme (weeks 5–7); T2—immediately postperformance (12–14 weeks); T3—immediately after the advocacy training for stroke ambassadors.

To maximise inclusivity and outcome completion, and minimise participant burden, outcome assessments, where possible, will be conducted either face-to-face, online, by telephone or via postal questionnaire depending on the outcome measures being assessed, participants’ preferences and government COVID-19 guidelines.

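### The planned before/after tests of AIM, IAM, FIM and EQ5D have no pre-intervention value to use, because Table 2 schedules none of the four at T0

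*Protocol article*

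**What the plan says.** Table 2 of the protocol article gives the primary implementation objective as "To evaluate to what extent SO is acceptable, to survivors and wider stakeholders". It is measured by AIM at T1, T2 and T3, with interviews at T2 and T3. The IAM and FIM rows carry the same survey schedule. The row for costs and quality of life places EQ5D and the service-use schedule (AD-SUS) at T2 and T3.

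The Outcomes section makes T0 the baseline and places T1 "midway through the 12-week programme (weeks 5–7". T2 follows the performance, at weeks 12 to 14. The last time point is "T3—immediately after the advocacy training for stroke ambassadors".

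The Quantitative analysis section plans three things:
- descriptive summaries of the survey data (distributions and averages);
- parametric and non-parametric tests to "compare the survey responses to the AIM, FIM, IAM and EQ5D before and after the SO intervention";
- generalised linear models of change in the same four instruments.

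Two other places bear on this. The Abstract's methods paragraph says participants are surveyed before and after each stage. The assessment descriptions for the implementation outcomes rely on service use and quality of life before and after the programme, and feed them into QALYs and cost-effectiveness.

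**The concern.** The analysis section names a contrast that the measurement schedule does not supply. Whoever runs it will have to substitute something, most likely T1 against T2. That compares people part-way through with the same people afterwards. Anyone who left before week 5 has no T1 score.

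There is also a mismatch of target. The primary implementation objective asks how acceptable the programme is, which is a level. A test of change does not estimate a level: stable high acceptability and stable low acceptability both give an expected difference of zero. Under a before/after label, a rise from T1 to T2 would look like a programme effect and no change would look like failure. Neither reading is justified.

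For EQ5D the stake is different. A change in quality of life over the programme needs a starting value, and the economic analysis is described as using one.

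**Working it through.** **Inputs.** Time points and schedules come from Table 2 and the Outcomes section; the planned tests come from Quantitative analysis; the sample sizes come from Sample size. The article gives no alpha, power, SD or target difference for these scales, so there is no power figure to reproduce. Its own counts do reproduce: 75 × (1 − 0.20) = 60 completing ambassador training, and 12 + 10 + 5 + 20 = 47 stakeholders.

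**Schedule against analysis.**

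| Instrument | T0 | T1 | T2 | T3 | Before/after test possible? |
|---|---|---|---|---|---|
| AIM | no | yes | yes | yes | no |
| IAM | no | yes | yes | yes | no |
| FIM | no | yes | yes | yes | no |
| EQ5D | no | no | yes | yes | no |

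T1 lies between 5/12 = 42% and 7/12 = 58% of the workshop stage. The available contrasts are T1–T2, T1–T3 and T2–T3 for the scales, and T2–T3 for EQ5D. All come after exposure has begun.

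**Could the missing T0 be a table error in the text?** Unlikely. The three scale rows are complete and agree with each other, and the adoption row of the same table does list T0, as does an interview row of Table 1. The primary-objective row of Table 1 is empty in the available text, so a separate EQ5D entry there cannot be ruled out. Table 2 is where EQ5D is visibly scheduled.

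**Stakeholders.** AIM also goes to deliverers, supporters and referrers, and the assessment descriptions add ambassadors. Of the 47 stakeholders, 20 are existing ambassadors, and the eligibility section requires ambassadors to have been through the training. They have no unexposed state to measure.

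**Can the level be estimated without a baseline?** Yes. For a proportion p, the half-width is 1.96·√(p(1−p)/n). Taking p = 0.80, which is an assumption:
- n = 75: 1.96·√(0.16/75) = 0.091
- n = 60: 1.96·√(0.16/60) = 0.101

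The 60 is the expected number completing ambassador training, used here only as an illustrative lower count; the article gives no expected number at T2.

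For a mean score the half-width is 1.96·SD/√n. With an assumed SD of 0.5 to 1.0 scale points it is 0.11 to 0.23 for n = 75 and 0.13 to 0.25 for n = 60.

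For the stakeholder groups, again at p = 0.80: 20 ambassadors 0.175, 12 carers 0.226, 10 clinical staff 0.248, 5 artists 0.351. The normal approximation is poor at these sizes (0.80 + 0.351 exceeds 1), so the figures show only that the intervals are wide.

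**The case against.** The strongest reply is that the same section already answers the objective. Averages and frequency distributions at T1, T2 and T3 describe how acceptable the programme is, and the interviews explore the reasons for the scores. This stands. A reader might infer that the primary implementation outcome is left without a usable analysis; the article does not support that.

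Second, the generalised linear models of change can be fitted to T1, T2 and T3. This also stands; only a before/after label would be wrong.

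Third, the error may lie in Table 2 and not in the analysis text, since the Abstract promises surveys before and after each stage. In addition, T2 to T3 does bracket the ambassador training, so a true before/after contrast exists for that one stage among those who train. Both points are fair. They mean the sections must be reconciled, without presuming which is at fault. They do not supply a value from before the whole programme.

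Fourth, an unseen analysis plan may fix the main time point and the intervals. It may, and their absence is not the complaint. The complaint is that two stated parts of the article disagree.

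Finally, no sample size, success threshold or stated decision rests on the before/after test of AIM. That limits the severity.

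**Conclusion.** The mismatch is real for all four instruments: on the Table 2 schedule, none has a value from before the programme, so the test as worded cannot be run. For AIM, IAM and FIM the named inferential analyses also address change when the primary implementation objective is a level. The practical harm is mislabelling: a mid-programme contrast could be reported as a programme effect. The descriptive answer to the objective remains valid, so this should be corrected but does not undermine the study.

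For EQ5D, the economic analysis described in the article depends on a starting value that Table 2 does not provide.

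The schedule comparison rests on the article alone, with the caveat above about the empty Table 1 row. The precision figures rest on the assumed 80% agreement and the assumed SD range; neither is in the article.

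**What to change.** **AIM, IAM and FIM.** In Quantitative analysis, replace the before/after test with:
- main estimate: the level of each scale at T2 with a 95% CI, among survivors with T2 data, stating how many are missing;
- stakeholder groups (5 to 20 people each) reported descriptively, with their wide intervals shown;
- secondary: the T1–T2–T3 change models, labelled as within-programme (during to after) change.

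This needs wording only and no new data. If the authors did intend a T0 measurement, Table 2 should say so and make clear that it records anticipated acceptability.

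**EQ5D and the service-use schedule.** Reconcile Table 2 with the Abstract, the assessment descriptions and Quantitative analysis. Either schedule a T0 assessment, which does mean new data but only one extra questionnaire at enrolment for up to 75 survivors, or drop the before/after claim. A baseline cannot be recovered for anyone who has already started the programme.

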#### Qualitative analysis

Initial analysis of qualitative data will be undertaken using an inductive approach to thematic analysis. All data from interviews and observations will be managed using NVivo V.10 and examined to categorise themes and key issues that emerge. Using this inductive approach, tentative theoretical explanations will be generated for each subgroup. Summary memos for data sets will be developed for each subgroup to provide the basis for within and between-group comparisons. The inductive approach is data driven; based on observation, the early analysis seeks to reveal patterns and themes from which tentative hypothesis can be drawn subsequently leading to theory; theories are devised to explain what is seen rather than the other way around.

CFIR (www.CFIR.org) will be used to further guide the coding and analysis (ie, framework analysis) of interview data to identify barriers and facilitators to the implementation and sustainment of the SO programme. This approach has been used previously, that is, CFIR has been applied postimplementation to investigate facilitators and barriers to implementation among stakeholders who had already adopted and implemented an innovation, thus identifying determinants of implementation posthoc.^26 27^

Reflective summaries: the relationship of the researcher(s) with the research context they are investigating will be presented in the form of a written narrative of ideas and experiences during data collection. These reflective summaries will be shared with the research team and externally to judge any possible biases with the way the data were collected or prior assumptions.

### Patient and public involvement

The programme has been developed and further refined using codesign methodologies with a group of 20 members of South London stroke communities. The project has been shared widely with stroke clinicians across London and has their full support. During the pandemic Rosetta Life set up an advisory group consisting of Stroke Ambassadors to support the redesign of the website www.strokeodysseys.org, to monitor how people living with the effects of a stroke were engaging with the online workshops, to oversee the development of the education videos and the Ambassadors Handbook.

This advisory group is now a stable and national network of ambassadors who curate an online programme and advise on the development and delivery of SO. They have advised the investigators on the need to ensure that the measures were aphasia friendly and found an organisation to make sure that the measures were aphasia friendly. They will now look at the language of the Implementation Science measures and make sure that they are accessible.

### Trial registration and current status

This study is registered on ClinicalTrials.gov PRS under the ClinicalTrials.gov. Recruitment was scheduled to start in Autumn 2021.

### Data protection

The investigator will ensure that this study is conducted in full conformity with relevant regulations and with the ICH Guidelines for Good Clinical Practice (CPMP/ICH/135/95) July 1996. The investigator will ensure that this study is conducted in accordance with the principles of the Declaration of Helsinki.

Access to person identifiable implementation science data will rest with the data custodian(s) from the immediate study team and the implementation science team. Since the project seeks to explore in some depth participants’ experiences and barriers and facilitators to implementation, it is important to maintain strict confidentiality and facilitate openness in the interviews and survey responses, thus optimal data quality.

Consent forms and audio/video recordings will be kept electronically in KCL’s SharePoint for the duration of the study, only accessible by the teams at KCL, Kingston University and Rosetta Life involved in the study. Consent forms and other identifiable paperwork will be kept in locked cabinets only accessible to the study team. Study data will be kept in a separate location from the person identifiable information. Access to the deidentified research data will be shared with the study management group for the purposes of review, analysis and dissemination. Only deidentified data will be analysed.

After the completion of the study, the study data will be kept for the King’s College London’s standard retention period of 10 years after the completion of the study. The study data that support published results will be deposited in a secure data repository (eg, King’s Research Data Management System). This will allow the data to be accessible for future reuse as per King’s College London’s policy on the management of research data long-term.

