### Intervention

SO is a poststroke performance art intervention designed and delivered by the arts organisation Rosetta Life. This intervention initially developed and funded by King’s and Guy’s & St Thomas’ Charity, aims to improve recovery, agency and well-being after stroke.^14^

SO comprises three distinct stages (1) weekly workshops conducted over 12 weeks for stroke participants which will be facilitated by an integrated team of expert artists and ‘stroke ambassadors’ from the charity Rosetta Life, (2) a smaller group of ambassadors recruited from the workshops will be trained to become cofacilitators (ie, new stroke ambassadors), (3) a performance tour including education and taster workshops for audiences.

During sessions, which run for 3 hours each, participants devise a dance and music performance work from their own stories. The practice of ‘performing ourselves’ is key to achieving successful outcomes such as transforming the participants’ perception of identity. The culmination of the programme will be a public-facing performance to an audience of carers, healthcare practitioners, friends, family and the wider community.

Due to the ongoing COVID-19 pandemic and the necessity of shielding vulnerable adults and foreseeing increased anxiety in stroke survivors to attend in-person sessions, we have adapted the SO programme to be delivered through a mixture of live/face-to-face and online delivery (blended approach). Participants will be able to choose whether to attend the sessions/participate face-to-face or online based on their personal preferences and needs. The researcher will manage groups to ensure that all the participants who wish to attend in person will be able to do so during the 12 weeks.

The adapted programme will still be run in three stages, described below:

Stage (1): the workshops are the result of cocreation; the general framework is: weeks 1–3 building the performance company, weeks 4–6 devising the performance weeks 6–9 rehearsing the performance and weeks 10–12 are sometimes concertinaed into one production week introducing stage management, lighting and technical runs. Each of the 12 workshops contains a performance ‘class’ of 20–30 mins exploring movement and voice techniques and exercise.

Participants will be able to choose whether to attend the sessions/participate face-to-face or online based on their personal preferences and needs.

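### The organisation that designed and delivers the programme is given access to audio/video recordings with no exception for interviews, which is not reconciled with the stated confidentiality aim

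*Protocol article*

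**What the plan says.** The Intervention section of the protocol article identifies the deliverer: "SO is a poststroke performance art intervention designed and delivered by the arts organisation Rosetta Life".

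Under Qualitative data collection, survivors are interviewed "to explore their attitudes towards the acceptability, appropriateness and feasibility of the programme". The same interviews cover what helped or hindered their involvement, possible drop-out and unintended consequences, and these issues are also explored with wider stakeholders. On recording, the article says: "Interviews will be audiotaped and are anticipated to be conducted 1:1 or in participants dyads".

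The Data protection section then makes two statements about access:

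- On identifiable data: "Access to person identifiable implementation science data will rest with the data custodian(s) from the immediate study team and the implementation science team". The reason given is that "it is important to maintain strict confidentiality and facilitate openness in the interviews and survey responses".
- In the following paragraph, consent forms and audio/video recordings are held on a university server, "only accessible by the teams at KCL, Kingston University and Rosetta Life involved in the study".

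The second statement does not separate interview recordings from any other kind. The first does not say who belongs to the immediate study team.

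**The concern.** The interviews ask people to judge a programme, and the organisation that designed and runs it is named among those who can open the recordings. A voice recording identifies the speaker. Under Recruitment procedure, Rosetta Life's project manager handles all referrals, so the organisation knows the survivors who take part.

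Interviewees who know that the deliverer can listen have a reason to soften criticism. Survivors may feel this at T2, straight after the performance, since ambassador training is offered once the performance is over. Artists and existing ambassadors have a continuing tie to the organisation.

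The interview findings are at stake. Table 2 uses interviews to explain the acceptability (primary), appropriateness and feasibility scores. It lists interviews alone for unintended consequences, for barriers and facilitators to implementation, and for barriers and facilitators to sustained use. For those objectives, Table 2 names no second source from which withheld criticism could be recovered.

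**Working it through.** No arithmetic bears on this point, because the article gives no figure from which a bias could be calculated. The check sets the statements side by side.

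**1. Are the interviews within the recordings covered by the access statement?** The statement covers both audio and video. Interviews are audiotaped and may be held remotely by phone or video. Workshop observations are captured as field notes. Performance screenings and education videos are mentioned elsewhere, so the recordings may include more than interviews. Nothing takes the interviews out, however, and they are the only audiotaping the article describes. As written, they are covered.

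**2. Do the two access statements agree?** That depends on the undefined term.

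| Reading of immediate study team | Consequence |
|---|---|
| Excludes Rosetta Life | The first statement keeps identifiable implementation data from Rosetta Life and the second grants it the recordings. The two conflict. |
| Includes Rosetta Life staff | The two agree on access, but the evaluated organisation can hear identifiable evaluations of its own programme. This works against the openness that the first paragraph sets out to protect. |

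The text needs correction on either reading.

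**3. Do other safeguards close the gap?** The implementation science team conducts the implementation interviews, study data are stored apart from identifiers, and only de-identified data are analysed. These govern who asks the questions and what is analysed. They do not govern who can open a recording.

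**4. Does the deliverer need the access?** Since the implementation science team does that interviewing, the article states no research task for which Rosetta Life must hear the interviews.

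**5. Which outcomes are exposed?**

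- Directly: the interview findings listed under the concern.
- Not directly: the AIM, appropriateness and feasibility scores. These come from questionnaires, and the Data protection section gives Rosetta Life no stated access to identifiable survey answers.

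**The case against.** The strongest reply is that there may be no contradiction. Access is limited to teams involved in the study, and if Rosetta Life's study staff belong to the immediate study team, the two statements are consistent. This stands against calling the text a flat contradiction. It does not remove the problem, because the confidentiality aim is then undercut instead.

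A second reply is that the recordings may be mainly performance footage. That is possible and the article does not settle it, but the wording as it stands includes the interviews.

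A third is that access arrangements and information-sheet wording belong in the full protocol. That would answer a complaint about missing detail. Here the article states an access rule, and the rule sits badly with an aim stated in the same section.

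Some stronger readings are tempting but unsupported:

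- A reader might infer that acceptability findings are biased upward. The mechanism requires interviewees to know of the access when they speak. The information sheet is not shown, and nothing establishes that bias occurs or how large it would be.
- A reader might extend the problem to the primary acceptability score. That score is a questionnaire result.
- A reader might measure exposure by the 5 artists and 20 existing ambassadors among the 47 planned stakeholders. Those are recruitment targets. Only a subsample is interviewed, and its make-up is not stated.
- A reader might conclude that interviews are the study's sole evidence on implementation. The Data collection section also assigns non-participant observations to experiences of the programme and its implementation, and reasons for drop-out are recorded under adherence. The claim holds only for what Table 2 lists against each objective.

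**Conclusion.** The point holds as an unreconciled pair of access statements that creates an avoidable risk of favourable bias in the interview findings. It rests on two readings of the text: that audio/video recordings include the audiotaped interviews, which nothing excludes, and that interviewees would know of the access, which the documents neither confirm nor rule out. The size of any bias cannot be derived, and the AIM score is not directly affected. The correction should be made because it is cheap and because the findings most exposed are those for which Table 2 lists no other source.

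**What to change.** Amend the Data protection section as follows:

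1. Define the immediate study team and bring the two access statements into line.
2. Restrict interview recordings and identifiable transcripts to university researchers who are independent of programme delivery.
3. Give Rosetta Life de-identified findings only.
4. Tell participants and stakeholders in the information sheet who can and cannot hear their interviews.
5. If workshops or performances are filmed, keep those files separately under their own access rule, so that the delivery partner can still use them.

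The cost is a change of folder permissions and a sentence or two in the protocol and the information sheet. The downside is that the delivery partner loses direct access to raw interview material.
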